### Outcome measures

The timeline for the outcome measures will be the baseline measurements, and the 3- and 6-month follow-ups after randomisation.

### Feasibility outcomes

The primary aim of this study is acceptability and feasibility of procedures for recruitment, allocation, measurement and retention as well as the adherence and enjoyment levels of the exercise programme. Recruitment rates will be assessed as the rate of invited patients who are eligible and consenting and will be reported in a CONSORT (Consolidated Standards of Reporting Trials) patient flowchart. Suitability of measurement procedures will be assessed via interviews and reasons for missing data. Reasons for dropouts will be used to evaluate the acceptability of allocation procedures and exercise programme. The acceptability of the exercise programme will also be assessed through questionnaires relevant to exercise task self-efficacy, intentions for engagement to exercise, enjoyment levels of exercise and the affect during exercise, and the physiological stress of exercise monitored by HR and RPE. The safety of exercise will be evaluated by the dropout number from the exercise group, and the number and type of adverse events.

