#### Withdrawals

Patients will be considered as withdrawn from the research trial if they request to leave the trial, if they are lost to follow-up or if they die before completing the 6-month follow-up.

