### Clinical management

All the patients in both studies will continue receiving their standard medical treatment, i.e. calcium channel blockers (nifedipine, sildenafil), and will be reviewed in the clinic as often as is deemed clinically necessary. Moreover, in case of adverse events or worsening of symptoms due to exercise or patients request, patients will be withdrawn from the study for health and safety reasons.

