### Safety monitoring

We will record all serious adverse events (as defined below), as well as all non-serious adverse events that are deemed to be related to participation in the research, during the period between the provision of informed consent through to 6 months after randomisation.

Serious adverse events are defined as any untoward medical occurrence that either results in death, is life-threatening (i.e. the patient is at risk of death at the time of the event occurring), requires unplanned admissions to emergency hospitalisations or prolonged hospitalisation (deemed to be where a patient’s stay is longer than expected, e.g. patient is operated on as a day case but remains in hospital overnight), results in persistent or significant disability or incapacitation, or results in a congenital abnormality or birth defect.

A non-serious event in the context of this trial will be any untoward medical occurrence to the participant that is related to the patients’ involvement in the study but does not fulfill any of the serious adverse event criteria.

Study investigators will be responsible for recording adverse events and for determining the seriousness, severity, causality and expectedness of any such events. The Chief Investigator (MK) and a delegated clinician (MA) will then be responsible for reviewing all adverse events and confirming that they have been appropriately classified.

A serious adverse event will be reported to the Research Ethics Committee and Sponsor where, in the opinion of the Chief Investigator and the delegated clinician, the event was related to the administration of a research procedure or resulted in death regardless of relatedness.

Patients will be asked to contact the study team to inform them about adverse events if and when they occur. Study investigators will also question patients about the occurrence of adverse events during each participant study visit.

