### Statistical analysis

The sample size for a feasibility study should be adequate to estimate the critical metrics needed to assess the feasibility of conducting the definitive study, with sufficient precision [34]. The critical metrics are the consent rate (i.e. the proportion of eligible patients who consent to participate and be randomised), improvement in microcirculation and quality of life as well as compliance with treatment, and attrition rates. Fifteen patients in each group (*n* = 30 in total) will provide a sufficiently precise (within 15 percentage points for a 90% confidence interval) estimate of the proportion willing to be randomised, assuming 35–40% intention to be randomised.

The SPSS software (version 23, IBM SPSS, New York, USA) will be used to enter quantitative data and cleaning the data and to carry out missing values imputation and statistical analysis. The descriptive statistics, including mean and standard deviation, will be presented for basic demographics and primary and secondary outcomes of the patients in intervention and control groups. For categorical data, the χ^2^ test will be used to infer on the significant association. Independent and paired samples *t* tests will be used to account for the changes upon the primary and secondary outcomes within the group at pre- and post-exercise intervention but also between the two groups. Kolmogorov–Smirnov and Shapiro–Wilk tests will be used to test the normal distribution of the dependent variable and Levene’s test will be used to test the homogeneity of variances. Pearson’s r will test any relations and interactions between our variables. The qualitative analysis will be performed using framework analysis [35], aiming to describe individuals’ experiences of exercise, searching for common, recurrent patterns but also exploring participant experiences that might explain behaviour and improve advice and services in the future. Data saturation will be achieved when similar themes arise repeatedly and no new themes arise in the interview.

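### The exercise-arm dropout number, one of two stated safety inputs, mixes ordinary attrition with harm and cannot by itself be read as safety evidence

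*Protocol article*

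**What the plan says.** The Feasibility outcomes section of the protocol article names two inputs to the safety assessment: "The safety of exercise will be evaluated by the dropout number from the exercise group, and the number and type of adverse events". The first is a plain count from one arm. Nothing in the sentence restricts it by cause or sets it against the control arm.

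Earlier in the same section, the recorded reasons are given a different use: "Reasons for dropouts will be used to evaluate the acceptability of allocation procedures and exercise programme".

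Two other sections determine who can enter the count:
- Withdrawals regards patients as withdrawn "if they request to leave the trial, if they are lost to follow-up or if they die before completing the 6-month follow-up". It does not list withdrawal because of harm.
- Clinical management states that "in case of adverse events or worsening of symptoms due to exercise or patients request, patients will be withdrawn from the study". Here harm and patient preference are grouped together.

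The Safety monitoring section supports the second safety input, and its opening sentence reads: "We will record all serious adverse events (as defined below), as well as all non-serious adverse events that are deemed to be related to participation". Investigators are responsible for "determining the seriousness, severity, causality and expectedness of any such events", and the classification is then reviewed.

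The Statistical analysis section plans for "Fifteen patients in each group". It names attrition as a critical metric but gives no expected value.

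**The concern.** A dropout count becomes safety evidence only when it is known why people left. Two visits a week for 12 weeks can lose patients through travel, work, illness unrelated to exercise or loss of interest. In the stated measure these losses count the same as a withdrawal because symptoms worsened. The information that would separate them is collected, but the text uses it for acceptability. The control arm, which would show background attrition, is not mentioned in the safety sentence.

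The risk lies in interpretation, and it runs both ways. Ordinary attrition could be reported as a safety worry. A low count could be reported as reassurance, although 15 exercised patients cannot exclude a sizeable harm rate. The Abstract says the data are meant to inform and support a multicentre trial, so a safety statement resting partly on this count would carry forward.

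**Working it through.** **Plan's own figure.** The article gives no number for safety or dropout. Its only precision statement concerns willingness to be randomised: within 15 percentage points, 90% confidence interval, n = 30, proportion 35% to 40%. The half-width is 1.645 × √(p(1−p)/n):
- p = 0.35: 1.645 × √(0.35 × 0.65/30) = 14.3 points
- p = 0.40: 1.645 × √(0.40 × 0.60/30) = 14.7 points

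The stated figure reproduces, but it does not bear on safety.

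**Inputs for the check.** The exercise arm has n = 15 (Statistical analysis). Ordinary, harm-free attrition b is assumed at 10% to 30%, and harm-related stopping h at 10% or 20%, because the article gives neither. If the two act independently, the combined rate is t = 1 − (1 − b)(1 − h).

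**Step 1: a harmless programme.** The number of dropouts X is binomial(15, b). Then P(X ≥ 1) = 1 − (1 − b)^15, and P(X ≥ 3) = 1 − P(0) − P(1) − P(2).

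| Assumed b | Expected dropouts | P(X ≥ 1) | P(X ≥ 3) |
|---|---|---|---|
| 10% | 1.5 | 79% | 18% |
| 15% | 2.25 | 91% | 40% |
| 20% | 3.0 | 96% | 60% |
| 30% | 4.5 | >99% | 87% |

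**Step 2: adding harm.** With b = 20% and h = 10%, t = 1 − 0.80 × 0.90 = 28%. P(X ≥ 4) rises from 35% to 64%. The count does respond to harm, but with heavy overlap.

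**Step 3: the order can reverse.** A safe programme with b = 30% expects 15 × 0.30 = 4.5 dropouts. A programme with b = 10% and h = 10% has t = 1 − 0.90 × 0.90 = 19% and expects 15 × 0.19 = 2.85. The harmful programme shows the smaller expected count.

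**Step 4: what an observed count supports.** The exact 95% interval for 3 of 15 is 4% to 48%, and it says nothing about cause.

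**Step 5: counting by cause.** If only harm-related stops are counted and causes are classified correctly, a harmless programme expects 0. P(at least one) is 1 − 0.90^15 = 79% when h = 10% and 1 − 0.80^15 = 96% when h = 20%. If none is seen in 15, the exact two-sided 95% upper limit is 1 − 0.025^(1/15) = 22%.

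**Step 6: would the control arm alone solve it?** It addresses attribution in principle. However, a test of all-cause dropout at 15 per arm has only about 6% to 24% power over b = 10% to 30% and h = 10% to 20%. Classification by cause does the work; the comparison between arms can only be descriptive.

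**The case against.** The strongest reply is that the dropout number is only half of the safety sentence. The other half is the number and type of adverse events, which Safety monitoring has assessed for seriousness and causality and then reviewed. Patients are also questioned about events at each study visit. This stands: the safety evaluation as a whole can tell harm from ordinary attrition.

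A reader might infer three stronger things that the article does not support:
- **That the count is unrelated to harm.** It is not. Clinical management leads from adverse events or worsening symptoms to withdrawal, so the count contains a harm signal diluted by other causes.
- **That every dropout will be read as harm.** The article does not say so, and it sets no dropout threshold for calling exercise unsafe. The cut-offs of 1, 3 and 4 used above are illustrative.
- **That reasons are barred from the safety reading.** They are assigned to acceptability, but nothing forbids wider use. All-cause describes the unrestricted wording; it is not a term in the article.

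It can also be said that control-arm attrition will be known anyway, since retention is a primary outcome. That is true, and it is why the repair is cheap.

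Finally, an unrestricted count has some value as a backstop. Non-serious events are recorded only if deemed related, investigators are not masked, and a patient who stops attending is hard to question. This also stands, so the total should be shown beside the cause-specific count and not deleted. The 22% upper limit for 0 of 15 follows from the sample size and applies to the proposed measure too, so it is no argument against the present wording.

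**Conclusion.** The point holds for the dropout component only. As worded, that component confounds ordinary attrition with harm-related withdrawal and is not interpretable as safety evidence on its own. The adverse-event component remains usable.

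The size depends on attrition that the article does not state: under an assumed 10% to 20% harm-free loss, the chance of three or more dropouts among 15 in a harmless programme is 18% to 60%. No sample size, hypothesis test or decision rule is affected. This is a modest defect in a descriptive measure of a feasibility trial. It is worth correcting because a better measure can be built from data already being collected.

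**What to change.** 1. **Feasibility outcomes.** Replace the exercise-arm dropout number as a safety input with the number of patients in each arm who stop the programme (exercise arm) or leave the trial because of an adverse event or worsening symptoms, taken from the recorded reasons. Report the exercise-arm proportion with an exact 95% interval, including the upper limit when the count is zero (about 22% for 0 of 15). Keep the number and type of adverse events as they are.
2. **Alongside it,** show all dropouts by cause in both arms, descriptively and without a between-arm test. State that the all-cause total is evidence on retention and acceptability.
3. **Withdrawals and Clinical management.** Reconcile the two sections, since one lists request, loss to follow-up and death and the other adds harm. The count then has one definition.

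The cost is a few sentences and one table row. No new data and no change of sample size are needed. The downside is that the safety statement will carry a visibly wide limit, which reflects what 15 patients can show.

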### Enjoyment and tolerance of exercise

The feasibility and the perceived enjoyment of HIIT and RT will be assessed through measures that will interpret patients’ perception regarding the (1) exercise intensity, (2) the affect, (3) the exercise task self-efficacy, (4) the intentions and (5) the enjoyment. The above data will be collected at the first and last exercise session each month in order to examine several time points during the exercise intervention. Specifically, the questionnaires will be administered at the 1st, 8th, 9th, 16th, 17th and 24th exercise sessions.

#### Exercise intensity

The RPE will be measured during exercise through a 20-point Borg scale [24] when 2.5%, 8.2%, 42.5%, 48.2%, 92.5% and 98.2% of the exercise programme is completed. These time points have been chosen to incorporate both interval and recovery periods during HIIT. In the RT, the time points will be straight after the completion of each exercise. The 20-point Borg scale ranges from 6 to 20 with anchors ranging from ‘No exertion at all’ (0) to ‘Maximal exertion’ [20]. Apart from measurement at the specified time points during exercise, the RPE will be measured pre- and post-exercise as well as 10 min after the exercise session. Participant’s HR will also be recorded using Polar HR monitors at the same time points as the RPE.

#### Affective valence

The one-item Feeling scale [25] will be used to measure the general affective valence (e.g. pleasure and displeasure) during the exercise session at the same time points as the RPE (Additional file 1). At the beginning of the first exercise session, patients will be provided with the following instructions: “Experiencing alterations in your mood is very common while performing exercise. The sense of pleasure or displeasure varies among individuals during the exercise; in addition, feelings may fluctuate across time. So the answers might feel good and bad a number of times during exercise, when you will be asked to express your feelings using the scale below”. The feeling scale is scored on an 11-point bipolar scale ranging from − 5 to + 5. Seven anchors are provided ranging from ‘Very good’ (+ 5) to ‘Very bad’ (− 5).

#### Exercise task self-efficacy

Patient’s confidence in their ability to repeat the exercise session that they will just have completed will be assessed only after the first exercise session at 20-min post-exercise using a three-item measure (Additional file 2). Each question will include the same introductory theme, “How confident are you that you can…”. The three-items will be (1) “… perform one bout of exercise a week for the next 4 weeks that is just like the one you completed today?”, (2) “… perform two bouts of exercise a week for the next 4 weeks that is just like the one you completed today?” and( 3) “… perform three bouts of exercise a week for the next 4 weeks that is just like the one you completed today?”. The scale score will vary from 0% (Not at all) to 100% (Extremely confident) in 10% increments. The specificity of the three items measure is formed and adapted according to Jung et al. [26].

#### Intentions

Patient’s intentions to engage in the exercise session over the next month will be measured utilising a two-item measure (Additional file 3) at the 1st, 9th and 17th exercise session, 20-min post-exercise [26]. Particularly, patients will be asked “Please rate the extent to which you agree with the following statements (1) ‘I intend to engage in the type of exercise I performed today at least 2 times per week during the next month’ and (2) ‘I intend to engage in the type of exercise I performed today at least 3 times per week during the next month’”. Answers will be scored on a 7-point rating scale with anchors ranging from ‘Very unlikely’ [1] to ‘Very likely’ [7]. The two items will be analysed individually.

#### Enjoyment

Patient’s enjoyment of the assessed exercise sessions will be examined using a modified version of the Physical Activity Enjoyment Scale [27] 20-min post-exercise. This 18-item measure is scored on a 7-point bipolar scale (Additional file 4). Example items are “I find it energising/I find it tiring” and “it’s very pleasant/it’s very unpleasant”. The original measure is amended by erasing one of the 18 items that is irrelevant due to the time point that will be measured (“I am absorbed in the activity/I am not at all absorbed in the activity”). Moreover, the original Physical Activity Enjoyment Scale instructions are amended from “Please rate how you feel AT THE MOMENT about the physical activity you have been doing” to “Please rate how you feel about the exercise you just completed”. Both modifications were made to reflect the correct time point at which the questions/questionnaire will be administered (20-min post-exercise).

### Patient experiences for study procedures

We aim to undertake an in-depth exploration of the patients’ study experience in a subsample of six patients from each group (exercise and control group). Interviews lasting between 30 and 35 min will take place 3 months after randomisation for both groups.

We aim to explore (1) patients’ experiences of RP; (2) experiences of treatment and advice received pre FESS trial; (3) participant’s preference for trial allocation (exercise or control group); (4) experiences of study participation in both the exercise intervention group and control group; and (5) participant’s acceptability of the exercise intervention and study procedures.

We will adopt a constructivist approach [28], which recognises the individual and personal nature of a patient’s exercise experiences both before and during the trial. Semi-structured face-to-face in-depth interviews will be conducted at the Centre for Sports and Exercise Science at Sheffield Hallam University in a comfortable and private room. Interviews will be recorded and then transcribed verbatim, and will then be analysed thematically by using framework analysis (familiarisation, identifying a thematic framework, indexing, charting and mapping).

Sample and recruitment

Six and six patients from exercise and control group, respectively, will be recruited using purposive sampling (mixture of sexes, younger and older patients from exercise and control group).

### Secondary outcomes

#### Digital cutaneous microvascular function

##### Iontophoresis

Microvascular assessments using LDF and iontophoresis (as described in the literature; [22]) will be performed in a temperature-controlled room (22–24 °C). LDF electrodes will be attached to the dorsal aspect of the reference fingers for acetylcholine (ACh) and sodium nitroprusside (SNP) administration. These will be used as indicators of the changes occurring in the endothelial (dependent and independent) vasodilatory function. HR (Sports Tester, Polar, Finland) and blood pressure of the brachial artery (left arm; Dinamap Dash 2500, GE Healthcare, USA) will be monitored at 5-min intervals throughout the protocol. The two drug delivery electrodes (PF383; Perimed AB, Jarfalla, Sweden) will be positioned over the healthy-looking skin, approximately 4 cm apart with one containing 100 μL of 1% ACh (Miochol-E, Novartis, Stein) and the other 80 μL of 1% SNP (Nitroprussiat, Rottapharm). A battery-powered iontophoresis controller (PeriIont PF382b; Perimed AB) will be used to provide the charge needed for ACh and SNP delivery. A 4 min stable recording of baseline flux will be followed by administration of the two agents according to the following protocol: 0.2 mA for 10 s (i.e. 2 mC), 0.2 mA for 15 s (i.e. 3 mC), 0.2 mA for 20 s (i.e. 4 mC), and 0.3 mA for 20 s (i.e. 6 mC), occurring between 4-min intervals [21, 22]. To obtain an index of skin blood flow, cutaneous red cell flux will be measured by placing an iontophoresis laser Doppler probe (PF481–1; Perimed AB), connected to a laser Doppler fluximeter (PF5001; Perimed AB).

##### Peak oxygen uptake test

During the cardiopulmonary tests, gas exchange will be collected and analysed by an online breath-by-breath analysis system (Ultima™, Medical Graphics, UK). The gas analyser will be calibrated before each test according to the manufacturer’s calibration guidelines. HR breathing frequency, tidal volume, minute ventilation, VO_2_ and volume of exhaled carbon dioxide, and their ratios, as well as the respiratory exchange ratio, will be displayed on a monitor (BreezeSuite, MGC Diagnostics, USA) on a breath-by-breath analysis. HR will be continuously monitored using a Polar HR monitor (Polar FS1, Polar Electro, Kemple, Finland) and blood pressure will be assessed by the researcher using a manual sphygmomanometer (DuraShock DS54, Welch Allyn, USA) and a stethoscope (Littman Classic II, 3 M, USA). The RPE will be recorded during the last 10 s of every minute during the exercise test until volitional exhaustion using Borg’s scale [24] with 6–20 points. Peak power output and test duration will be measured in both tests. VO_2peak_ will be defined as the average oxygen consumption recorded from expiratory samples during the final 30 s of exercise.

##### Arm crank ergometer protocol

The arm crank ergometer will be adjusted to ensure alignment between the ergometer’s crankshaft and the centre of the glenohumeral joint. The patient’s sitting position will also ensure that the elbows are slightly bent when the arm is outstretched and will be instructed to maintain their feet flat on the floor at all times. Due to different power capabilities, two different protocols will be instructed for men and women. Men will commence at a workload of 40 W and women at 20 W. In both protocols, the crank rate will be maintained at 70 rev min^− 1^ [29] and the linear ramp increments will be increased by 1 W/6 s and 1 W/10 s for men and women, respectively [30]. The test will commence with 2 min resting and 2 min of warm-up unloaded. A RPE of 18 or above and/or the inability to maintain a crank rate above 60 rev min^–1^, or if any contraindication signs emerge [31] will result in the termination of the test. Following termination of the exercise part of the test, an unloaded exercise will be performed for 2–3 min allowing an active cool down.

